# Implementation and evaluation of a multi-professional care pathway and network for the promotion of needs-oriented, resident-oriented exercise therapy for oncological patients (MOVE-ONKO): protocol of a mixed-methods cohort study

**DOI:** 10.1186/s12885-025-13797-7

**Published:** 2025-03-13

**Keywords:** Cancer, Care pathway, Exercise therapy, Evaluation, Implementation

## Abstract

**Background:**

Physical activity has been shown to be beneficial for people diagnosed with cancer. MOVE-ONKO aims at implementing a new multiprofessional care pathway in 3 large regions in Germany at the interface of oncological treatment and exercise therapy for cancer patients. The related study aims to evaluate the implementation processes and patient outcomes.

**Methods:**

The project comprises 3 phases: 1) preparation, 2) implementation in Comprehensive Cancer Centres (CCCs), 3) implementation in remote cancer centres. In phase 1, individual prerequisites for the implementation are assessed in the participating CCCs. The care pathway which is supported by digital/app-based exercise oncology health record is developed and adapted to the CCCs. Phases 2 and 3 focus on the implementation and evaluation of the care pathway.

To study the effectiveness, primarily changes in patients' health-related quality of life are examined in a prospective design. Secondary outcomes include physical activity behaviour, motivation for physical activity and patient activation. A sample of 2240 cancer patients ≥ 18 years (*n* = 280 patients at seven CCCs in phase 2 and *n* = 1.960 patients at the seven CCCs and 49 remote oncological centres in phase 3) are recruited for assessment at inclusion and at 4, 12 and 24 weeks.

The newly implemented care structures and processes will be assessed from the perspective of key informants, healthcare providers and patients. The perspectives of key informants on the implementation from the CCCs will be recorded in a prospective design based on a questionnaire and supplemented by in-depth semi-structured interviews across the three phases. The implementation processes are documented by assessing existing structures in CCCs. In phase 2 (*n* = 105) and phase 3 (*n* = 350), healthcare providers will be surveyed with questionnaires. Based on purposeful sampling (*n* = 18) will be interviewed. Additionally, qualitative patient interviews will be conducted about their experiences in the care pathway.

**Discussion:**

A successful implementation of the care pathway as part of the study will contribute to the growing evidence on the implementation of a nationwide structured approach to exercise therapy for patients with cancer.

**Trial registration:**

ClinicalTrials.gov (ClinicalTrials Identifier NCT06185777) at December 29, 2023.

## Background

Interventions to enhance regular physical activity, especially as systematic and needs-based exercise therapy, have proven to be an effective supportive care element for people diagnosed with cancer in all stages of the disease, as shown in more than 700 randomized controlled trials with about 50.000 patients [1, 2]. International guidelines and consensus recommendations [1, 3, 4] call for multiprofessional approaches to promote physical activity in cancer patients and propose ways to plan and carry out needs-based exercise therapy. In Germany, exercise therapy for cancer patients is recommended in S3 guidelines for supportive therapy for prostate and breast cancer [5–7]. Despite the overwhelming evidence, concepts and implementation strategies to integrate exercise therapy and physical activity counselling into oncological care remain sparse [1–3, 8–11].

Several barriers for implementing exercise therapy have been identified: foremost, integrating exercise therapy in acute oncological care and access to exercise therapy programmes due to lack of funding and counselling resources. The integration of exercise therapy comprises early information and physical activity counselling. General recommendations for exercise are challenged by the individual needs and capabilities of patients, which are related to symptoms of the disease, side effects of the oncological treatment and individual preferences [1, 4, 12]. Therefore, healthcare providers need to consider the individual situation of the cancer patient in physical activity counselling. Many healthcare providers lack competencies to inform patients about exercise therapy. Additionally, time is limited in the busy clinical schedule [10, 13]. Healthcare providers often underestimate patients’ resources and capabilities and are unaware of available information and experts for exercise therapy within their healthcare organization [11, 14, 15]. Activity-focused conversations are postponed or omitted forfeiting shared decision-making for supportive exercise therapy. Thus, the adoption of physically-active behaviour by cancer patients is limited [14, 16, 17].

Additionally, adequate exercise therapy programmes of high quality are often not available or easily accessible for all patients. These barriers were also assessed in a recent study in Germany evaluating a network providing exercise therapy [18]. Other barriers identified were complexity of certification for exercise therapy in oncology and missing network structures, travel time for patients, missing referrals, and lack of knowledge of healthcare staff as well as missing certification and lack of knowledge of exercise therapists without specialisation in cancer.

Therefore, the aim of the MOVE-ONKO project is to implement and evaluate a healthcare delivery model to connect cancer patients with exercise therapy which is based on their individual needs and abilities. A structured approach—the MOVE-ONKO care pathway—identifies eligible cancer patients and provides information and guidance on evidence-based individual physical activity.

## Description of the MOVE-ONKO care pathway

The care pathway (Fig. 1) describes a desired series of steps that patients follow during healthcare delivery, covering initial screening, followed by a brief counselling session to gain patients’ awareness and an intensive physical activity counselling. The pathway becomes part of healthcare delivery and is the intervention that is implemented in this project. At the same time, it is a strategy to implement evidence-based physical activity interventions in cancer care.

**Fig. 1 Fig1:**
[figure not shown]
MOVE-ONKO care pathway

Patients are included into the pathway at the start or during the delivery of cancer treatment (medication, radiation, surgery, or combinations of these). They are approached by exercise oncology guides (EOGs). EOGs are oncology professionals with direct patient contact (e.g. in day clinics, oncology outpatient clinics or consultations). Patients can also be referred by physicians or other specialists; patients may also approach EOGs independently. The need for exercise therapy is determined on the basis of screening questions regarding fatigue, psychological stress, polyneuropathy, physical functioning, quality of life as well as on the basis of patients’ interest. If a patient is eligible, a detailed exercise-related history is taken, followed by a brief counselling session. The next step is by a risk assessment (modified risk assessment according to the National Comprehensive Cancer Network (NCCN) criteria and the American College of Sport Medicine (ACSM) pre-participation screening [19]) based on the clinical data collected.

If no risk factors, such as serious comorbidities or complex symptoms that are critical in relation to exercise therapy, are present, an EOG advises the patient on how to proceed. If risk factors or a more comprehensive counselling request are present, further counselling is provided by an exercise oncology specialist (EOS). The EOSs are exercise therapy professionals (exercise physiologist/scientists or sports physicians), who receive training in oncological content developed as part of the MOVE-ONKO project prior to the start of patient recruitment.

Based on individualised recommendations made during the physical activity counselling, patients are recommended to attend a specific exercise therapy option, such as structured exercise therapy programmes or community-based physical activity services, and virtual exercise therapy programmes by using the MOVE-ONKO APP. EOGs and EOSs refer patients to exercise therapy programmes by contacting local exercise therapy or physical activity options.

The care pathway is supported by the digital/app-based exercise oncology health record (MOVE-ONKO APP) which is used by EOGs and EOSs to guide them through the care pathway and to collect exercise therapy relevant clinical data. Thus, the MOVE-ONKO APP provides a common platform for patient files. The APP can also be used by patients to communicate with therapists and vice versa, especially when patients use the MOVE-ONKO APP-based exercise therapy programme. Additionally, a web-based information platform provides general information about cancer and physical activity as well as integrates an existing search platform to local exercise therapy services. There will be further support and feedback between these centres and researchers to support the implementation of MOVE-ONKO.

## Aims and research questions

The evaluation of the MOVE-ONKO care pathway focusses on the effectiveness of the intervention (intervention aim) and the uptake of the pathway by professionals and patients (implementation aim). Intervention success will be observed in benefits of physical activity and exercise therapy for the patients (e.g. better physical functioning). Implementation success as well as structures and processes for a long-term and sustainable implementation will be explored from the perspectives of patients, key informants and healthcare providers.

The evaluation research focusses on the following research questions:

Evaluation of intervention outcomes.How do patient-reported experiences and outcomes develop in patients enrolled in the MOVE-ONKO care pathway?

Evaluation of implementation processes.To what extent can the planned MOVE-ONKO intervention be implemented in phases 2 and 3 in the CCCs and remote cancer centres?Which barriers and facilitators determine the implementation in phases 2 and 3 of the MOVE-ONKO intervention?Which resources guarantee/predict sustainable implementation in phase 2 and phase 3 of the MOVE-ONKO intervention?To what extent does the MOVE-ONKO intervention increase the reach of the care pathway and the utilisation of exercise therapy by patients?

## Methods

### Logic model

The AIMD framework [20] was used to guide the evaluation. According to the framework aims, components, mechanisms of the intervention and delivery mode of the intervention are summarised in a logic model (Fig. 2). In order to consider the specific circumstances of the different participating centres, we have added a contextual component. The logic model of the MOVE-ONKO project was created in an iterative process involving programme developers and evaluators.

**Fig. 2 Fig2:**
[figure not shown]
Logic model based on AIMD

### Study design

The prospective observational mixed-methods study (without control arm) will combine perspectives of key informants, healthcare providers and patients based on survey data and in-depth semi-structured interviews.

The study comprises three phases (Fig. 3): 1) preparation, 2) implementation in seven Comprehensive Cancer Centres (CCCs) in three large regions in Germany, 3) implementation in remote cancer centres.

**Fig. 3 Fig3:**
[figure not shown]
Evaluation design

The care pathway will be developed in phase 1 and adapted to the CCCs. Additionally, specific prerequisites of the participating CCCs will be assessed. Phases 2 and 3 focus on the implementation of the care pathway. In phase 2, the care pathway will be implemented in seven CCCs; phase 3 will additionally include remote oncological centres associated with the regional CCCs. These can be organ-specific cancer centres or ambulatory oncological care organisations. The evaluation in both phases focuses on intervention outcomes and implementation processes. Intervention outcomes relate to patients’ reports on quality of life, physical activity and other outcomes. Implementation processes are examined from the perspectives of key informants, healthcare providers and patients.

## Evaluation of intervention outcomes

To observe intervention outcomes, a longitudinal prospective study without control group evaluates patient outcomes before, during and after the implementation of the care pathway. Patients receive questionnaires either electronically or paper-based at inclusion of the study before receiving physical activity counselling (t0), 4 weeks (t1), 12 weeks (t2) and 24 weeks (t3) after inclusion (Fig. 3).

### Participants and recruitment

Eligible for participation are cancer patients, at least 18 years old, with all cancer types regardless of the stage of the disease and during acute treatment. They show symptoms related to the disease or the treatment which have been shown to be positively impacted by exercise therapy (i.e. fatigue, emotional strain, polyneuropathy, reduced physical functioning, reduced quality of life) and/or they are interested in exercise therapy. Patients are included at all stages of their cancer treatment.

Patients are recruited for the study at the start or during the delivery of cancer treatment (medication, radiation, surgery, or combinations of these). They are approached by EOGs or referred by physicians or other specialists, patients may also approach EOGs or EOSs independently. Patients are informed about the study and the MOVE-ONKO care pathway. If they consent to participate in the study, they are asked to fill in the first survey and are enrolled in the MOVE-ONKO care pathway. Participation in the MOVE-ONKO care pathway involves participating in the study. There are no further incentives for the patients.

### Measures

Intervention outcomes are addressed in patient questionnaires comprising the European Organisation for Research and Treatment of Cancer Quality of Life Questionnaire (EORTC QLQ-C30 [21], primary outcome: subscale Physical functioning), the Godin-Shepard Leisure-Time Physical Activity Questionnaire [22], and a questionnaire to assess Physical Activity-Related Health Competence (PAHCO [23]) (Table 1). Additionally, sociodemographic characteristics, motivation for physical activity, social support, patient activation, experiences with the care pathway, patient involvement and shared decision making, and adherence to exercise therapy are assessed. Patient questionnaires will be pretested for practicability to avoid overstretching of participating cancer patients’ time and energy.

**Table 1 Tab1:** Patient survey measures and data collection times

Outcome	Measure	Data collection time			
		Baseline (t0)	4-week follow-up (t1)	12-week follow-up (t2)	24-week follow-up (t3)
Physical functioning and quality of life	EORTC QLQ-C30 [21]	x		x	
	EORTC QLQ item bank items	x		x	x
Physical activity	Godin-Shephard Leisure Time Physical Activity Questionnaire [22]	x	x	x	x
Physical activity-related health competence	PAHCO questionnaire [23]	x	x	x	x
Motivation for physical activity (behaviour change)	HAPA Stages assessment: stage, duration of behaviour pattern performance	x	x	x	x
	HAPA Stages assessment: outcome expectancy	x		x	
	HAPA Stages assessment: intention	x		x	x
	HAPA Stages assessment: plans		x	x	x
Self-concordance of sport- and physical activity-related goals	SSK [24]	x	x	x	x
Social support	BS6 [25]	x			
Patient activation	PAM [26]	x		x	
Care assessment	PACIC (adapted) [27, 28]	x		x	
Experiences with MOVE-ONKO care pathway	PEACS (adapted) [29]		x		
Patient involvement and shared decision making	SDM-Q-9 (adapted) [30]		x		

*BS6* Brief Social Support Scale, *EORTC QLQ-C30* European Organisation for Research and Treatment of Cancer Quality of Life Questionnaire Core 30, *PAHCO* Physical Activity-related Health Competence, *HAPA* Health Action Process Approach, *PACIC* Patient Assessment of Chronic Illness Care, *PAM* Patient Activation Measure, *PEACS* Patients’ Experiences Across Health Care Sectors, *SDM-Q-9* Shared Decision-Making Questionnaire; t0 Baseline, t1 4-week follow-up, t2 12-week follow-up, t3 24-week follow-up

### Sample size calculation

The intervention is anticipated to cause a change in the subscale Physical functioning of the EORTC QLQ-C30 during the three-month intervention period between t0 and t2, with an effect size (ES) = 0.3 in repeated measures design. In phase 2, participants will be recruited across seven CCCs, and analyses will be performed across all centres. In phase 3, there will be 49 peripheral centres in addition to the seven CCCs. This brings up the total number of recruitment centres to 56 that will involve patients in the MOVE-ONKO care pathway and its evaluation. The following assumptions are considered: power = 0.80, intra-subject correlation = 0.5, intraclass correlation (ICC) = 0.01 (patients in centres), and drop-out = 10%. To demonstrate an effect of 0.3 between t0 and t2, a total of approximately 280 patients are required from seven centres (*n* = 40 per centre) in phase 2. In phase 3, around 1,960 patients are needed from 56 centres.

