#### Data analysis

Quantitative data are analysed using IBM SPSS 27 (or newer). Questionnaire scales are summarised according to the respective test manual guidelines. Variables are described as frequencies (categorical variables) or mean with standard deviation (metric variables). Differences between observations in the primary outcome (physical functioning) are analysed using a linear model with the value of physical functioning at t2 as dependent variable and its value at t0 as independent variable and adjusting for the cluster structure of the data (different centres) and patient characteristics (age, gender, education). Missing values will be replaced by multiple imputation. An additional sensitivity analysis will only use complete cases. Estimated parameters, *p* values and confidence intervals are reported. *P* values smaller than 0.05 will be considered statistically significant.

Other quantitative outcomes are analysed using the same analysis scheme as for the primary outcome.

The audio recordings of all individual interviews will be transcribed and pseudonymised. The transcripts will be analysed using the MAXQDA Analytics Pro software, following the structuring qualitative content analysis method by Kuckartz [41]. Two researchers will independently code and finally analysed by consensus. Main categories will be developed based on the interview guideline, and inductive subcategories will be developed during the coding process.

The results of the quantitative and qualitative surveys are finally brought together in evaluation workshops (triangulation).

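### The stated sample-size assumptions yield neither 280 nor 1,960 patients: both figures exceed what they require, and what 1,960 is sized for is not said

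*Protocol article*

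**What the plan says.** In the protocol article, under Evaluation of intervention outcomes, Sample size calculation, the primary outcome (EORTC QLQ-C30 Physical functioning, change from t0 to t2) is planned "with an effect size (ES) = 0.3 in repeated measures design". The listed assumptions are "power = 0.80, intra-subject correlation = 0.5, intraclass correlation (ICC) = 0.01 (patients in centres), and drop-out = 10" per cent. From these the section concludes that "a total of approximately 280 patients are required from seven centres", at 40 per centre, in phase 2. It then states: "In phase 3, around 1,960 patients are needed from 56 centres".

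The section gives no formula, no design effect and no separate target for phase 3. It says that phase 2 will be analysed across all centres, and makes no such statement for phase 3. Alpha does not appear there. The Data analysis section supplies it: P "values smaller than 0.05 will be considered statistically significant", with sidedness not stated.

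**The concern.** The paragraph presents one set of assumptions and two results as if the results followed from them. Two features suggest that they do not.

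- 280 looks large for a within-patient comparison with an effect of 0.3 and a correlation of 0.5.
- Moving from seven to 56 centres lowers the number per centre from 40 to 35 (1,960/56). With the ICC fixed, this lowers the design effect, so a pooled requirement for the same effect should fall slightly. The stated figure rises sevenfold.

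This paragraph is the statistical justification for asking 2,240 patients under acute cancer treatment to complete repeated questionnaires. If its inputs and outputs disagree, a reader cannot tell which assumption was used, what power the study has, or what phase 3 is sized to answer.

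**Working it through.** **Inputs.** From Sample size calculation: effect 0.3, power 0.80, intra-subject correlation r = 0.5, ICC 0.01, drop-out 10%, 40 per centre in phase 2, 1,960/56 = 35 per centre in phase 3. From Data analysis: alpha 0.05, taken as two-sided. I apply the ICC to the change score.

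**Step 1, unclustered size.** The standardised paired effect is 0.3/√(2(1 − r)) = 0.3/√1 = 0.3. At r = 0.5 it therefore does not matter whether 0.3 is in units of the SD of scores or of change. The normal formula gives (1.960 + 0.842)²/0.3² = 87.2, so 88. The noncentral t gives 90.

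**Step 2, phase 2.** Design effect 1 + (40 − 1) × 0.01 = 1.39. Then 90 × 1.39 = 125.1, and 125.1/0.9 = 139. The stated 280 is not reproduced: 280/139 = 2.0.

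Other conventions move this figure:
- Fixing seven centres and solving 7m/(1 + 0.01(m − 1)) = 90 gives m = 14.6, so 102.2 analysed and 102.2/0.9 = 113.6 enrolled.
- A centre-level t test with 6 degrees of freedom needs 22 analysed per centre, so 154 analysed and 172 enrolled (175 with whole patients per centre, 25 × 7).

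The range is about 114 to 175, so 280 is 1.6 to 2.5 times the requirement.

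**Step 3, phase 3 as one pooled analysis.** Design effect 1 + (35 − 1) × 0.01 = 1.34. Then 90 × 1.34/0.9 = 134, and 1,960/134 = 14.6. Solving for patients per centre with 56 centres fixed gives 1.62 per centre, 90.6 analysed and about 100 enrolled. I also varied the inputs: one-sided alpha, power 0.90, alpha 0.025 or 0.01, ICC 0.02, r = 0. No pooled variant exceeded 491.

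**Step 4, where the figures may come from.** If the correlation is left out (r = 0), the paired effect is 0.3/√2 = 0.212 and the t-based size is 177. Then 177 × 1.39/0.9 = 273.4, or 39.05 per centre. Rounding up to 40 per centre gives exactly 280. For phase 3, 1,960 = 7 × 280 = 7 × 8 × 35: seven networks, each of one CCC and seven remote centres, at 35 per centre. On that reading the comparison per network is 280 against 134, a ratio of 2.1.

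**Step 5, what the stated numbers deliver with r = 0.5.**

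| Enrolled | Analysed | Per centre | Design effect | Effective n | Power for 0.3 | Effect at 80% power |
|---|---|---|---|---|---|---|
| 280, 7 centres | 252 | 36 | 1.35 | 186.7 | 98% (92% with 6 df) | 0.21 SD (0.25 with 6 df) |
| 1,960, 56 centres pooled | 1,764 | 31.5 | 1.305 | 1,351.7 | above 99.9% | 0.08 SD |

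Power is Φ(0.3√n_eff − 1.96), and the detectable effect is 2.80/√n_eff: 2.80/√186.7 = 0.205 and 2.80/√1,351.7 = 0.076. The 6-df values use the noncentral t.

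**The case against.** The strongest reply is that the error is on the safe side and that both figures are traceable. Leaving out a within-patient correlation is a conservative choice, and with rounding to 40 per centre it lands exactly on 280. The figure 1,960 fits seven networks of eight centres. The roll-out to 56 centres may also be reason enough for the size, and the full protocol, not shown here, may say so. Much of this stands, but it does not reconcile the paragraph. The correlation is listed as an assumption that entered the calculation, and no network-level analysis is mentioned. Nor is this a matter of condensing: inputs and results are both printed, and they disagree.

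Three stronger readings are tempting, and the document does not support them.

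- A reader might infer that the 80% power claim fails. It is understated: power under the stated inputs is higher.
- A reader might take a 14-fold excess in phase 3 as established. It depends on one pooled analysis for the same target. Pooling is stated for phase 2 only, and the sentence naming the target of 0.3 gives the phase 2 number.
- A reader might infer that trivial changes will be declared a success. The article gives no SD and no minimal important difference, so triviality cannot be shown. The Data analysis section sets a significance level, not a success rule, and already plans confidence intervals.

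**Conclusion.** The point holds as a mismatch between stated inputs and stated results. For phase 2 the inputs require about 139 patients (about 114 to 175), against 280 described as required. For phase 3 they require about 134 (about 100 if cluster size is solved for), against 1,960 described as needed, if the analysis is pooled. If phase 3 was sized per network, the excess is again about twofold.

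The conclusion rests on two-sided alpha 0.05, on the ICC applying to the change, and on a test of mean change. The planned model regresses the t2 value on the t0 value, but the sample-size section speaks of a repeated-measures effect.

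That there is no shortfall also depends on the stated inputs. If r were truly 0 and a 6-df test were used, about 436 to 441 patients would be needed for seven centres. This is why it matters to know which correlation the authors relied on.

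**What to change.** Keep recruitment unchanged and correct the Sample size calculation paragraph:

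- Show the formula, including alpha, its sidedness and the design effect, and say whether the intra-subject correlation of 0.5 was used. If it was not, remove it from the list or recompute with it.
- Restate what the numbers deliver under the listed inputs. For 280: about 92–98% power for 0.3, or 80% power for about 0.21–0.25 SD. For 1,960 pooled: more than 99.9% power for 0.3, or 80% power for about 0.08 SD.
- State what 1,960 is sized for, for example 280 per CCC network or roll-out to 56 centres, instead of presenting it as the number needed to show 0.3. Say whether phase 3 is analysed pooled or by network.

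The cost is the rewording of one paragraph, with no change to recruitment or data collection.
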